## **7.2 Randomization Process**

Subjects screened in this study will be sequentially granted a three digit study number. For each study number a randomization envelope is supplied indicating the treatment assigned for both Treatment Phase I and Treatment Phase II. Treatment should be given in the order listed in the randomization envelop. The bottles are labelled as “J” and “K” from the supplier who knows the content of each bottle. Study staff and study subjects will be blinded as to study treatment being given: the probiotics or placebo.

# **8 STUDY PROCEDURES**

## **8.1 Visit Schedules**

### ***Screening and Visit 1 – Day 1***

At Visit 1 subjects who sign the Informed Consent Form and the Consent for Donation and Storage of Patient Samples for Research Tests form will be allocated a two digit screening number e.g. 01, 02, 03 etc. The screening number must be assigned in sequence and must not be skipped. Screening numbers may not be reassigned for any reason.

Each subject screened in the study will also be identified by three letters: the first initial of the first name, the first initial of the middle name (if the subject does not have a middle name, a dash should be inserted) and the first initial of the family name.

Before any study-related procedures are done, the subject must participate in the informed consent process and sign the Informed Consent Form.

The following assessments will be performed at Visit 1:

- Inclusion and exclusion criteria will be reviewed;
- Medical health history will be evaluated;
- A vaginal health questionnaire will be completed;
- Review concomitant medications; and
- One (1) vaginal swab will be taken to determine Nugent Score (see section 8.2(v)).

Subjects who have met the inclusion and exclusion criteria will continue in the study.

Enrolled subjects will have the following assessments performed:

- Four (4) additional vaginal samples will be taken during this visit in the following order (see section 8.2(i–iv)):
  - one swab for multiplex immunologic analysis;
  - one cytobrush sample for metabolomic analysis;
  - one cytobrush sample to evaluate host gene regulation;
  - one swab for microbiota analysis; and

- A vaginal pH measurement will be taken with a vaginal pH indicator strip, pHem Alert.

Subjects will be given a diary to rate general vaginal discomfort and record any other adverse events. An appointment will be scheduled to return in 4 days (5 days is acceptable) for Visit 2.

Subjects with an intermediate Nugent Score may or may not exhibit signs of a vaginal infection such as itching, burning during urination, and/or an abnormal or foul-smelling discharge.

### ***Visit 2- Day 5 (+ 1 day)***

The following assessments will be performed:

- Subject diaries will be reviewed and subjects queried regarding any adverse events the subject may have experienced;
- A vaginal health questionnaire will be completed;
- Five (5) vaginal samples in the following order:
  - one swab for Nugent Score/microbiota analysis;
  - one swab for multiplex immunologic analysis;
  - one cytobrush sample for metabolomic analysis;
  - one cytobrush sample to evaluate host gene regulation;
  - one swab for microbiota analysis;
- A vaginal pH measurement will be taken in the same manner as described for Visit 1;
- Review concomitant medications; and
- An appointment will be scheduled for Day 15 visit.

### ***Treatment Phase I - Visit 3 – Day 15 (+/-2 days)***

The following assessments will be performed:

- Subject diaries will be collected and reviewed, and subjects queried regarding any adverse events they may have experienced;
- A vaginal health questionnaire will be completed;
- Five (5) vaginal samples and a vaginal pH measurement will be taken in the same manner as described for Visit 2;
- Randomize subjects with Nugent Scores between four (4) and six (6) as per section 7.2;
- Subjects with a Nugent Score ranging from four (4) to six (6) will be given either six (6) placebo or six (6) probiotic capsules per the randomization and will be instructed to administer them vaginally twice daily, one in the morning and one in the evening, for the next 3 consecutive days. Written instructions for product administration will be provided. Panty liners will be supplied to use on treatment days;
- Subjects will be instructed to keep the capsules in the container and refrigerated between 4°C and 6°C until use;
- Diaries will be dispensed to track compliance and to rate any general vaginal discomfort and record any other adverse events;
- Review concomitant medications; and

- An appointment will be scheduled to return in 4 days (5 days is acceptable) for the Day 19 visit.

*Subjects with a Nugent Score of 7 – 10 at Visit 3 will be treated for Bacterial Vaginosis (BV) as deemed appropriate by the Investigator and discontinued from the study. End of treatment assessments and procedures (Visit 8) should be done.*

*Subjects with a Nugent Score of 0 – 3 at Visit 3 will be asked to return in 7 days (+/-1 day) to have the Nugent Score reassessed. If subjects continue to have a Nugent Score of 0 – 3 after one week, they will be discontinued from the study. End of treatment assessments and procedures (Visit 8) should be done.*

#### **Visit 4 – Day 19 (+1 day)**

Subjects will return to the clinic four (4) days after Visit 3. The following assessments will be performed:

- Subject diaries will be reviewed and subjects queried regarding any adverse events they may have experienced;
- A vaginal health questionnaire will be completed;
- Five (5) vaginal samples and a vaginal pH measurement will be taken in the same manner as described for Visit 2;
- Subjects' diaries will be returned to the subjects to rate general vaginal discomfort and record any other adverse events daily until their next visit;
- Review concomitant medications; and
- An appointment will be scheduled for Day 26 visit.

#### **Visit 5 – Day 26 (+/- 1 day)**

Subjects will return to the clinic seven (7) days after Visit 4. The following assessments will be performed:

- Subject diaries will be collected and reviewed and subject will be queried regarding any adverse events they may have experienced;
- A vaginal health questionnaire will be completed;
- Five (5) vaginal samples and a vaginal pH measurement will be taken in the same manner as described for Visit 2;
- Review concomitant medications; and
- An appointment will be scheduled for Day 36 visit.

#### **Treatment Phase II - Visit 6 – Day 36 (+/-2 days)**

The following assessments will be performed:

- Subjects will be queried regarding any adverse events they may have experienced;
- A vaginal health questionnaire will be completed;
- Five (5) vaginal samples and a vaginal pH measurement will be taken in the same manner as described for Visit 2;

- Subjects that have a Nugent Score of 4 – 6 will then be given either six (6) placebo or six (6) probiotic capsules per the randomization and will be instructed to administer them vaginally two (2) times daily for the next 3 consecutive days. Written instructions for product administration will be provided. Panty liners will be supplied to use on treatment days;
- Subjects will be instructed to keep the capsules in the container and refrigerated until use;
- Subjects will be given a diary to track compliance and to rate any general vaginal discomfort and record any other adverse events;
- Review concomitant medications; and
- An appointment will be scheduled to return in 4 days (5 days is acceptable) for Day 40 visit.

*Subjects with a Nugent Score of 7 – 10 at Visit 6 will be treated for BV as appropriate by the Investigator and discontinued from the study. End of treatment assessments and procedures (Visit 8) should be done.*

*Subjects with a Nugent Score of 0 – 3 at Visit 6 will be discontinued from treatment. If these subjects are still colonized with at least one of the probiotic strains they will return for a final study visit on Day 129. All subjects discontinued from treatment will be queried via telephone regarding adverse events on a monthly basis until Day 129.*

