**KEY:**

- Subjects with a Nugent Score of 4-6 will be given six (6) capsules to be inserted vaginally twice per day for the next three (3) days. Subjects with a Nugent Score of 7-10 will be treated for BV as appropriate and discontinued from the study. Subjects with a Nugent Score of 0-3 should return in one week to have the Nugent Score reassessed.
- Subjects with a Nugent Score of 4-6 will be given six (6) capsules to be inserted vaginally twice per day for the next three (3) days. Subjects with a Nugent Score of 7-10 will be treated for BV as appropriate and discontinued from the study. Subjects with a Nugent Score of 0-3 will be discontinued from treatment but will be followed until day 129.
- Swabs for microbiota analysis will also be used to assess colonization by probiotic strains on Visits 6, 8, and 9. Microbiota analysis will not be performed at Visit 9.
- Subjects who are not colonized with the probiotic strains at Visit 8 are not required to attend Visit 9, but will receive monthly AE telephone monitoring.

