#### **5.1.3 Diagnosis**

Clinicians consider the Nugent scoring system, first described in 1991, as the gold standard for diagnosing BV. Nugent diagnosis relies on the detection of vaginal epithelial cells infected by coccobacilli, the so-called "clue cells", upon microscopic examination of a Gram-stained smear of vaginal discharge.

The Nugent Score is calculated by assessing for the presence of:

- Large gram-positive rods (lactobacilli; Scored as 0 to 4);
- Small gram-variable rods (Scored as 0 to 4); and
- Curved gram-variable rods (Scored as 0 to 2).

The Nugent Score can range from 0 to 10 with a Score of >7 consistent with BV and a Score from 4 to 6 indicative of an intermediate microbiota. A Nugent Score from 0 to 3 indicates a normal status. Women with an intermediate Score have an approximately equal probability of developing either BV or a normal microbiota.

Using the “Amsel” set of clinical criteria in combination with the Nugent scoring system provides a simple and reliable tool for confirming BV presence. According to Amsel criteria BV may be defined by the following clinical signs:

- Vaginal pH >4.5;
- Presence of adherent white discharge;
- Detection of “clue cells”; and
- Presence of an amine odour after the addition of KOH treatment.

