# **10 CONCOMITANT MEDICATIONS AND TREATMENTS**

## **10.1 Rescue Medication for BV**

Currently, antibiotics represent the treatment of choice for BV and these may be administered either orally or topically as detailed below:

Oral: Metronidazole 500 mg twice daily for 7 days;

Topical: Clindamycin 2% cream, 5 g daily for 7 days.

At any time during the study where a subject presents with a Nugent Score of 7 – 10, the subject will be treated for BV as deemed appropriate by the treating physician. Subjects requiring antibiotic treatment will be discontinued from the study.

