#### **13.1.1 Analysis Populations**

**Safety Set:** All randomized subjects who received the INHP at any dose or placebo, will be included in the safety analyses.

**Full Analysis Set:** All randomized subjects will be analyzed following the principle of intention-to-treat (ITT) provided they received the INHP or placebo and had at least one efficacy observation after first insertion.

**Per protocol Set:** All subjects who are compliant with the study protocol (i.e., who do not experience any major protocol deviations), who received the INHP or placebo and had at least one efficacy observation after first insertion.

The primary efficacy analysis will be based on the Full Analysis Set, although a secondary analysis will also be performed based upon the Per-Protocol Set (if there are differences) to assess the sensitivity of the analysis to the choice of analysis population.

The analyses of all other efficacy endpoints will be based upon the Full Analysis Set only. All safety analyses will be based upon the Safety Set.

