##### **13.1.2.1 Nugent Score Analysis**

$$H_0: \pi_A = \pi_P$$

$$H_a: \pi_A \neq \pi_P$$

$\pi_A$  denotes proportion of subjects used intravaginal probiotic capsules had shown improvement in Nugent Score from intermediate (4-6) to normal status (0-3)

$\pi_P$  denotes proportion of subjects used intravaginal placebo capsules had shown improvement in Nugent Score from intermediate (4-6) to normal status (0-3)

McNemar's test will be utilized to test the hypothesis at 5% level of significance, 2-sided.

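### The primary McNemar test needs both phases, but the Visit 6 rule removes women from it because of their Nugent Score

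*Protocol*

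**What the plan says.** Section 13.1.2.1 compares the proportions moving from 4-6 to 0-3 on probiotic and on placebo: "McNemar's test will be utilized to test the hypothesis at 5% level of significance, 2-sided". The pair comes from the crossover. Section 7.2 states: "For each study number a randomization envelope is supplied indicating the treatment assigned for both Treatment Phase I and Treatment Phase II".

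Section 13.1.1 bases the primary analysis on the Full Analysis Set, which takes in randomised women "provided they received the INHP or placebo and had at least one efficacy observation after first insertion". One phase is enough to qualify.

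Section 8.1 (Visit 6, Day 36) gives Phase II capsules only to women who score 4-6 that day. For the others:
- **Score 0-3:** "Subjects with a Nugent Score of 0 – 3 at Visit 6 will be discontinued from treatment". The key to the visit schedule agrees: "Subjects with a Nugent Score of 0-3 will be discontinued from treatment but will be followed until day 129".
- **Score 7-10:** they are treated for BV and leave the study. Section 10.1 applies the same rule to such a score at any visit: "Subjects requiring antibiotic treatment will be discontinued from the study".

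The protocol does not say how a Full Analysis Set member without a second phase enters the McNemar table. Section 13.2 states that no formal sample size calculation was done for the 14 women.

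**The concern.** Three fixed parts of the protocol do not fit together: a paired test, an analysis set that accepts unpaired women, and a treatment rule that leaves women unpaired according to their score.

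This differs from ordinary dropout, because a Visit 6 score of 0-3 is the state that the primary endpoint counts as success. A Phase I success that fades by Day 36 stays in the test, and one that lasts is removed. If the probiotic works, the removals fall mainly on probiotic successes in the probiotic-first sequence.

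At stake are the number of usable pairs out of 14 and the direction of the estimated difference. A later analysis plan can say how to treat these women, but it cannot supply Phase II outcomes that were never observed.

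**Working it through.** **Inputs from the protocol:** McNemar, two-sided 5% (13.1.2.1); 14 women (13.2); the Visit 6 rule (8.1). The protocol states no power or effect size, so there is no figure to reproduce.

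**Assumed inputs:** 60% response on probiotic and 20% on placebo; 7 women per sequence; between-woman variation of SD 1.5 on the logit scale. Loss cases are written as responders still at 0-3 at Visit 6 / non-responders outside 4-6 at Visit 6.

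**1. Smallest result that can reject.** When all d discordant pairs go one way, the exact p is 2 × 0.5^d. For d = 5 it is 0.0625 and for d = 6 it is 0.031, so the exact test needs at least 6 discordant pairs. Uncorrected chi-square rejects with 4 (p = 0.0455).

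**2. Expected complete pairs.** Per sequence this is 7 × [p(1 − persist) + (1 − p)(1 − out)]. At 70%/20%:
- Probiotic-first: 7 × (0.6 × 0.3 + 0.4 × 0.8) = 7 × 0.50 = 3.5
- Placebo-first: 7 × (0.2 × 0.3 + 0.8 × 0.8) = 7 × 0.70 = 4.9
- Total: 8.4 of 14

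**3. Power by simulation.** The last column is a randomisation test over sequence that uses every observed phase (see the fix).

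| Persist / out | Mean pairs | Fewer than 6 discordant | Exact McNemar | Chi-square McNemar | Randomisation test |
|---|---|---|---|---|---|
| none lost | 14 | 28% | 46% | 68% | about 55% |
| 10% / 0% | 13.4 | 34% | 41% | 66% | 55% |
| 30% / 10% | 11.5 | 55% | 27% | 57% | 51% |
| 70% / 20% | 8.4 | 88% | 7% | 35% | 42% |
| 90% / 30% | 6.4 | 97% | 1% | 17% | 37% |

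Repeat runs differ by about a point (chi-square 65% and 16% in the mildest and most extreme loss cases). At 80% vs 30% response, exact power runs 71%, 66%, 49%, 16% and 3%. A separate calculation with 60% vs 10% response, independent phases and 10% of non-responders out of range gave 67% with no loss, 34% at 50% persistence and 4% at 100%.

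**4. Bias when persistence differs.** Take 70% persistence on probiotic, 30% on placebo and 20% of non-responders out of range, with the two phases independent for simplicity.
- Probiotic-first: kept 0.6 × 0.3 + 0.4 × 0.8 = 0.50, or 3.5 pairs. Success among those kept is 0.18/0.50 = 0.36, so the difference is 0.36 − 0.20 = 0.16.
- Placebo-first: kept 0.2 × 0.7 + 0.8 × 0.8 = 0.78, or 5.46 pairs. Success among those kept is 0.14/0.78 = 0.179, so the difference is 0.60 − 0.179 = 0.421.
- Pooled: (3.5 × 0.16 + 5.46 × 0.421)/8.96 = 0.32, against a true 0.40.

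With SD 1.5 the simulated value is 33 points. Equal persistence shifts the estimate less: 46 points against 50 in the 60% vs 10% calculation at 50% persistence.

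**5. False positives on complete pairs.** Response was set equal on both products (30% or 50%), with persistence from 50/50 to 90/10. Exact McNemar rejected at most 1.1%. Uncorrected chi-square reached 6.4% with a 7+7 split and 9.6% with 10 vs 4.

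**6. Scoring an absent Phase II as not improved.** With 50% response on both products and 90% vs 10% persistence, this creates a spurious 13 points in favour of the probiotic.

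**The case against.** **The rates are assumed, and the text gives reasons to expect mild loss.** The primary objective asks for one week of maintenance after a three-day course, and an 18-day washout follows. Section 5.3.2.2 says detection of the strains declines with time. Women must score 4-6 at Visit 1 and again before treatment, which partly screens out unstable flora. This stands: at 10%/0% the cost is 5 points of exact power and about 2 points for chi-square.

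**A reader might infer that the protocol predicts heavy loss.** Section 5.1.3 says "Women with an intermediate Score have an approximately equal probability of developing either BV or a normal microbiota", and Visit 6 plans for women at 0-3 with "If these subjects are still colonized with at least one of the probiotic strains". The first is background with no time frame. The second is a contingency. Both show that leaving 4-6 is possible, but neither says how often it happens by Day 36.

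**The study is an exploratory pilot with no power claim.** That limits the consequence. It does not remove the mismatch, since the protocol still sets a primary test at 5%.

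**Handling of incomplete pairs belongs in the analysis plan.** Partly so, and Section 13.1 requires one before first enrolment. But the test, the analysis set and the Visit 6 rule are all fixed in the protocol.

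**A reader might infer that McNemar must be replaced.** The figures do not support that. Section 13.1.2.1 does not say which version applies, and chi-square McNemar beats the randomisation test in the two milder loss cases. About 9 points of the randomisation test's gain over exact McNemar exist with no women lost (55% vs 46%), so they come from the discreteness of the exact test.

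**Conclusion.** The mismatch is real and worth correcting. Women in the primary analysis set leave the primary test because of their score, including women whose score meets the success definition. The loss of pairs follows directly from the text. Bias against the probiotic follows if its responses last longer than placebo responses.

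The size cannot be taken from the documents. Under the assumed 60% vs 20% response, exact power ranges from 41% (mild loss) to 1% (extreme loss), against 46% with all pairs. The 7-point bias rests on the assumed 70% vs 30% persistence.

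Two stronger conclusions are not supported. The trial is not invalid: exact McNemar showed no false-positive inflation in the cases run. Nor should the Visit 6 gate be dropped: the endpoint needs a 4-6 baseline, and BV needs antibiotics, which the study forbids.

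**What to change.** Keep the Visit 6 gate and change Section 13.1.2.1 as follows:

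1. State that McNemar is applied to complete pairs, and that the Visit 6 score selects those pairs. Name the version, exact or mid-p, since uncorrected chi-square can exceed 5% when persistence differs strongly.
2. Pre-specify the Phase I probiotic-placebo difference in all treated women, with an exact interval, as the estimate free of Visit 6 selection. Say that it is imprecise: 4/7 vs 1/7 gives an exact 95% interval of −11 to +81 points, and Fisher's test has about 15% power under the assumed 60% vs 20%.
3. Add, as supportive, a randomisation test over sequence that uses every observed subject-phase, stratified by phase and, within Phase II, by Phase I outcome. With equal response but unequal persistence it rejected 1.7-4.0% in the cases run; without the Phase I outcome split it reached as much as 13.5%. The sponsor may make it primary, knowing that against chi-square McNemar its power advantage appears only under heavy persistence.
4. Do not score an absent Phase II as not improved.

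The cost is protocol wording and a short program, with no extra women or visits. The downsides are slightly more analysis work and an imprecise Phase I estimate. The supportive test is also less familiar, is exact only if the products do not differ at all, and in Phase II still includes only women eligible at Visit 6.

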#### **Follow-Up Phase - Visit 7 – Day 40 (+1 day)**

The following assessments will be performed:

- Subject diaries will be reviewed and subjects queried regarding any adverse events they may have experienced;
- A vaginal health questionnaire will be completed;
- Five (5) vaginal samples and a vaginal pH measurement will be taken in the same manner as described for Visit 2;
- Subjects' diaries will be returned to them to rate general vaginal discomfort and record any other adverse events daily until their next visit;
- Review concomitant medications; and
- An appointment will be scheduled for Day 47 visit.

#### **Visit 8 – Day 47 (+/-2 days)**

The following assessments will be performed:

- Subject diaries will be collected and reviewed and subjects will be queried regarding any adverse events they may have experienced;
- A vaginal health questionnaire will be completed;
- Five (5) vaginal samples and a vaginal pH measurement will be taken in the same manner as described for Visit 2; and
- Review concomitant medications.

**Visit 9 – Day 129 (+/-7 days) Additional Follow-Up**

Subjects who are still colonized with at least one of the probiotic strains at Visit 8 (or at Visit 6 if they discontinued treatment at that time) will return for a final study visit. The following assessments will be performed:

- Subject will be queried regarding any adverse events they may have experienced; and
- One (1) vaginal swab will be taken in the same manner as the microbiota swab described in Section 8.2. This swab will not be used to perform the microbiota analysis however; the swab will only be used to determine whether the subject continues to be colonized by the probiotic.

Follow-up will be conducted for all treated subjects (including those that were discontinued). All treated subjects will be queried via telephone regarding adverse events on a monthly basis until Day 129.

